**7.2.1 Definitions**

An adverse event is defined as any untoward or unfavorable medical occurrence in a human research study participant, including any abnormal sign (for example, abnormal physical exam, imaging finding or clinically significant laboratory finding), symptom, clinical event, or disease, temporally associated with the subject's participation in the research, whether or not it is considered related to the subject's participation in the research.

Adverse events encompass clinical, physical and psychological harms. Adverse events occur most commonly in the context of biomedical research, although on occasion, they can occur in the context of social and behavioral research. Adverse events may be expected or unexpected.

Acute Adverse Events

Adverse events occurring in the time period from the delivery of radiation, through 90 days post treatment will be considered acute adverse events. *Adverse events will only be captured from medical oncology, radiation oncology, and surgical oncology clinic notes.*

***A dose- limiting toxicity (DLT) is a grade 3 toxicity deemed definitely related to treatment in the following categories: skin, rib bone (fracture), pulmonary (radiation pneumonitis), or neurological (intercostal or brachial plexus nerves) or any grade 4 or 5 toxicity deemed definitely attributed to the therapy.***

The following acute (<90 days) and late (>90 days – 36 months) toxicities definitely related to protocol treatment, as defined in CTCAE v5.0 will be reported

Grade 4 or higher toxicity in the below categories:

- Rib fracture
- Skin
- Radiation pneumonitis
- Neurologic
- Fat necrosis

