#### Late Adverse Events

Adverse events occurring in the time period from the end of acute monitoring (90 days), to 36 months/3 years post treatment, will be defined as late adverse events. After the 90 day acute period, we will only follow for grade 2 or higher toxicity: skin, rib/bone, bone (fracture), pulmonary (radiation pneumonitis), or neurological (intercostal or brachial plexus nerves) or any grade 4 or 5 toxicity deemed definitely attributed to the therapy. ***Adverse events will only be captured from medical oncology, radiation oncology, and surgical oncology clinic notes.***

***A dose- limiting toxicity (DLT) is a grade 3 toxicity deemed definitely related to treatment in the following categories: skin, rib bone (fracture), pulmonary (radiation pneumonitis), or neurological (intercostal or brachial plexus nerves) or any grade 4 or 5 toxicity deemed definitely attributed to the therapy.***

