### **7.3.1 Reporting SAEs and UPIRSOs to the Simmons Comprehensive Cancer Center (SCCC) Data Safety Monitoring Committee (DSMC)**

SAEs and UPIRSOs at all sites, which occur in research subjects on protocols for which the SCCC is the DSMC of record require reporting to the DSMC regardless of whether IRB reporting is required. All SAEs occurring during the protocol-specified monitoring period and all UPIRSOs should be submitted to the SCCC DSMC within 5 business days of the study team members awareness of the event(s). In addition, for participating centers other than UTSW, local IRB guidance should be followed for local reporting of serious adverse events or unanticipated problems.

The UTSW study PI is responsible for ensuring SAEs/UPIRSOs are submitted to the SCCC DSMC Coordinator. This may be facilitated by the IIT project manager, study team, sub-site or other designee. Electronic versions of the eIRB Reportable Event report; FDA Form #3500A forms, or other sponsor forms, if applicable; and/or any other supporting documentation available should be submitted to the DSMC.

UT Southwestern and affiliates will submit documentation via the SAE submission portal (InfoReady). The DSMC Coordinator will route the form to the DSMC Chair who determines if immediate action is required. Follow-up eIRB reports, and all subsequent SAE or UPIRSO documentation that is available are also submitted to the DSMC Chair who determines if further action is required via the same process. (*See Appendix V of the SCCC DSMC Plan for instructions on how to submit SAEs through the portal.*)

If the event occurs on a multi-institutional clinical trial coordinated by the UTSW Simmons Comprehensive Cancer Center, the IIT Project Manager or designee ensures that all participating sites are notified of the event and resulting action, according to FDA guidance for expedited reporting. DSMC Chair reviews all SAEs and UPIRSOs upon receipt from the DSMC Coordinator. The DSMC Chair determines whether action is required and either takes action immediately, convenes a special DSMC session

(physical or electronic), or defers the action until a regularly scheduled DSMC meeting.

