## 10.0 STATISTICAL CONSIDERATIONS

### 10.1 Study Design/Study Endpoints

#### Primary Endpoint

The primary endpoint of the phase I portion is to either reach the maximum tolerated dose (MTD) or a dose of 38 Gy total (whichever comes first) by escalating the dose of SBRT toward the tumorcidal dose of 38 Gy in fraction. Patients will be treated in cohorts of seven to fifteen. Toxicity will be graded using the NCI Common Toxicity Criteria for Adverse Events (CTCAE) v. 5.0. ***A dose-limiting toxicity (DLT) is a grade 3 toxicity deemed definitely related to treatment in the following categories: skin, rib bone (fracture), pulmonary (radiation pneumonitis), or neurological (intercostal or brachial plexus nerves) or any grade 4 or 5 toxicity deemed definitely attributed to the therapy.*** All reported DLTs will be verified by study chair, data and safety monitoring committee, and, as appropriate, independent review before final determination that a DLT has in fact occurred. Doses will be escalated an additional 3.5-4 Gy per treatment. The phase I portion of the study will be completed when either of the following events occur: 1) the MTD for a cohort is reached or 2) when delivery of a pre-determined highest dose of radiation (38 Gy) that has been deemed likely to be efficacious for treatment of early stage breast cancer is attained.

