### **11.4.3 Trial Audits**

Toxicity reviews will be performed annually from the day of the first patient enrollment, and dose escalation and/or de-escalation will be performed at the time of dose escalation and/or de-escalation on this study. The report will be stored in the digital regulatory repository.

The UTSW Simmons Comprehensive Cancer Center (SCCC) Data Safety Monitoring Committee (DSMC) is responsible for monitoring data quality and patient safety for all UTSW SCCC clinical trials. As part of that responsibility, the SCCC DSMC reviews all serious adverse events and UPIRSOs in real time as they are reported and reviews adverse events on a quarterly basis. The quality assurance activity for the Clinical Research Office provides for periodic auditing of clinical research documents to ensure data integrity and regulatory compliance. A copy of the DSMC plan is available upon request.

The SCCC DSMC meets quarterly and conducts annual comprehensive reviews of ongoing clinical trials, for which it serves as the DSMC of record. The Quality Assurance Coordinator (QAC) works as part of the DSMC to conduct regular audits based on the level of risk. Audit findings are reviewed at the next available DSMC meeting. In this way, frequency of DSMC monitoring is dependent upon the level of risk. Risk level is determined by the DSMC Chair and a number of factors such as the phase of the study; the type of investigational agent, device or intervention being studied; and monitoring required to ensure the safety of study subjects based on the associated risks of the study. Protocol-specific DSMC plans must be consistent with these principles.

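### The reporting list in Section 7.2.1 starts at grade 4 while a DLT starts at grade 3, so a non-serious grade 3 DLT has no event-triggered route to the DSMC that must verify it

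*Protocol*

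**What the plan says.** - **DLT definition (Sections 2.4, 7.2.1 and 10.1).** The event that counts "is a grade 3 toxicity deemed definitely related to treatment in the following categories: skin, rib bone (fracture), pulmonary (radiation pneumonitis), or neurological". Outside those categories, an event counts only at grade 4 or 5, again if definitely attributed to treatment.
- **Reporting list (Section 7.2.1, directly after that definition).** Acute and late "toxicities definitely related to protocol treatment, as defined in CTCAE v5.0 will be reported", and the list that follows is headed "Grade 4 or higher toxicity in the below categories". Its entries are fat necrosis and the same four categories. No recipient or deadline is given.
- **Late period (Section 7.2.1, Late Adverse Events).** After day 90, "we will only follow for grade 2 or higher toxicity" in the named categories.
- **Verification (Sections 2.4 and 10.1).** "All reported DLTs will be verified by study chair, data and safety monitoring committee, and, as appropriate, independent review before final determination". No deadline is set.
- **Expedited route (Section 7.3.1).** "All SAEs occurring during the protocol-specified monitoring period and all UPIRSOs should be submitted to the SCCC DSMC within 5 business days", counted from when the team learns of the event.
- **Routine review (Section 11.4.3).** The DSMC "reviews adverse events on a quarterly basis". Toxicity reviews are annual, followed by a garbled clause: "dose escalation and/or de-escalation will be performed at the time of dose escalation and/or de-escalation on this study".
- **Escalation rule (Section 10.1).** Escalate on 0/7, or on at most 2/9, 3/12 or 4/15 DLTs with 90-day follow-up. The MTD is exceeded at 3/9, 4/12 or 5/15. Neither the escalation paragraph nor the waiting-period paragraph mentions DSMC verification.

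**The concern.** The four organ categories matter to the DLT definition only at grade 3, because a definitely attributed grade 4 or 5 event is a DLT in any category. A reporting list that repeats these categories but starts at grade 4 therefore omits the events for which they were named. The wording has consequences because verification in Sections 2.4 and 10.1 applies to DLTs that have been reported, and Section 7.2 separates documenting an event from reporting it.

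At stake is the independent check on the primary endpoint. A cohort is cleared or stopped on very few events. A grade 3 DLT that nobody outside the study team has reviewed by the time of the decision leaves that decision without the verification the protocol calls for.

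**Working it through.** **1. The grade thresholds side by side**

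| Purpose | Lowest grade in the skin, rib, pulmonary and nerve categories | Where |
|---|---|---|
| Documented, consent to day 90 | any | 7.2, note |
| Followed after day 90 | 2 | 7.2.1, Late Adverse Events |
| Counts as a DLT | 3 | 2.4, 7.2.1, 10.1 |
| On the list to be reported | 4 | 7.2.1 |

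The DLT and reporting thresholds differ by one grade for the same categories and the same attribution (definite). Nothing in the protocol reconciles them.

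**2. Routes to the DSMC for a grade 3 DLT**

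- *SAE, 5 business days.* There is no grade limit. The event qualifies through hospitalization, disability or medical judgment, among other criteria (7.2.1). A grade 3 event managed without admission may meet none of them.
- *UPIRSO, 5 business days.* The event must be unexpected (7.2.2 and 7.3.1). Section 7.1 names skin toxicity, rib fracture and pneumonitis as adverse reactions, which points towards expected. Step 4 of Section 7.3 uses other sources, so this is not settled.
- *Quarterly review of adverse events (11.4.3).* This is scheduled and has no grade limit, but it is not linked to the escalation date and can fall after it.
- *Review at escalation (11.4.3).* The garbled clause may intend one. It names no reviewer and does not require DSMC sign-off.

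A grade 3 DLT that is neither an SAE nor a UPIRSO therefore has a periodic route only, with no event-triggered one.

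**3. The plan's own boundaries**

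3/9 = 4/12 = 5/15 = 33.3%, which agrees with the stated 33%.

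**4. What one uncounted DLT would do**

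Inputs: the cut-offs in Section 10.1 and an assumed true DLT rate p. A cohort with 0/7 can reach at most 2/9, and the nine-patient step as written always decides. So P(escalate) = P(X ≤ 2), with X binomial (9, p).

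At p = 0.33: 0.67^9 + 9(0.33)(0.67^8) + 36(0.33²)(0.67^7) = 0.385.

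If one DLT were always missing from the count, a true 3/9 would read as 2/9 and P(escalate) would become P(X ≤ 3):

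| True rate p | P(X ≤ 2), all counted | P(X = 3) | P(X ≤ 3), one always missing |
|---|---|---|---|
| 0.20 | 0.738 | 0.176 | 0.914 |
| 0.33 | 0.385 | 0.273 | 0.659 |
| 0.40 | 0.232 | 0.251 | 0.483 |

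**5. The seven-patient step**

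A true 1/7 read as 0/7 permits escalation at once. Correctly counted, the cohort would go on to nine, and the outcome would differ only if both of the next two patients had a DLT: p² = 0.33² = 0.109, about 11%. In the other 89% or so the dose would have been escalated anyway, only later.

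**The case against.** The strongest reply is that the escalation rule does not run on the grade 4 list. Section 10.1 counts patients who experience a DLT as defined there, from grade 3. All acute events are documented whatever their grade (7.2). Toxicity evaluation including DLT is scheduled at 1 and 3 months (5.4). The study summary names a single centre, so the team applying the rule holds the data. The list names no recipient, includes fat necrosis, which is not a grade 3 DLT category, and runs to 36 months. It is nowhere described as the gate for counting DLTs. All of this stands, and it limits the consequence to verification.

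Some stronger readings are tempting but not supported:

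- *That the DSMC has no scheduled sight of such an event.* It has the quarterly review.
- *That only grade 4 or higher events ever reach the DSMC.* SAE and UPIRSO reporting has no grade limit.
- *That a pending event counts as no DLT.* Sections 2.4 and 10.1 say only that verification precedes final determination. One could equally say that a cohort with a pending event has not gone 90 days without a DLT.
- *That a known number of extra patients would be treated during the delay.* The protocol gives no accrual rate, and a single DLT does not stop enrolment under Section 10.1, so most of those patients would be treated in any case.

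The reply does not remove the conflict between the list and the definition, and it supplies neither a deadline nor a verification step before escalation.

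**Conclusion.** The point holds as a contradiction within Section 7.2.1 and a gap in DSMC oversight. The list omits grade 3 DLTs. One that is neither an SAE nor a UPIRSO has no event-triggered route to the DSMC, and the protocol does not require verification before escalation.

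A reader might infer that the MTD will be biased upward. The documents do not support that, because the event should still be documented and counted by the study team. The table in step 4 shows how sensitive the rule is if a count were wrong, not what the protocol makes likely. It rests on an assumed true rate and on exactly one DLT always being missing. Under those assumptions the direct reversal is 3/9 read as 2/9, and at a rate of 33% the chance of escalating rises by 0.273. Reading 1/7 as 0/7 mostly just brings escalation forward.

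**What to change.** 1. **Section 7.2.1:** reconcile the reporting list with the protocol's own DLT definition, keeping fat necrosis as listed.
2. **Section 7.3.1:** add suspected DLTs to the existing 5-business-day report to the DSMC, whether or not they are SAEs.
3. **Sections 10.1 and 11.4.3:** reconcile the verification sentence, the escalation and waiting-period paragraphs, and the garbled review clause, so that pending DLT verifications are completed before an escalation decision.

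Whether a suspected DLT should count provisionally until it is overturned is a policy choice for the sponsor and is not part of this fix.

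The cost is a few sentences in an amendment, a few extra expedited reports, and an occasional short hold on escalation while an event is verified. No dose, decision boundary or sample size changes.

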#### Late Adverse Events

Adverse events occurring in the time period from the end of acute monitoring (90 days), to 36 months/3 years post treatment, will be defined as late adverse events. After the 90 day acute period, we will only follow for grade 2 or higher toxicity: skin, rib/bone, bone (fracture), pulmonary (radiation pneumonitis), or neurological (intercostal or brachial plexus nerves) or any grade 4 or 5 toxicity deemed definitely attributed to the therapy. ***Adverse events will only be captured from medical oncology, radiation oncology, and surgical oncology clinic notes.***

***A dose- limiting toxicity (DLT) is a grade 3 toxicity deemed definitely related to treatment in the following categories: skin, rib bone (fracture), pulmonary (radiation pneumonitis), or neurological (intercostal or brachial plexus nerves) or any grade 4 or 5 toxicity deemed definitely attributed to the therapy.***

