UTSW has been one of the pioneers in the S-PBI technique. Some adjuvant S-PBI retrospective reports published 30Gy/5Fx as a feasible dose (Vermeulen Front Oncol 2011; Vermeulen Transl Cancer Res 2014; Obayomi-Davies Front Oncol 2016). Specifically, 21 patients were treated with 25-36Gy/5-10Fx at the Swedish Medical Center, 26 patients treated with 30Gy/5Fx at Winthrop University (Vermeulen Transl Cancer Res 2014), and an additional 10 patients were treated with 30Gy/5Fx at Georgetown (Obayomi-Davies Front Oncol 2016). All of the patients in these cohorts reported good or excellent cosmetic outcomes, and none reported grade 3 or higher toxicity. These experiences suggested that 30Gy/5Fx was a safe and feasible dose, which led to a subsequent dose escalation trial at the University of Texas Southwestern (UTSW) noting that 40Gy/5Fx was biologically equivalent to the conventional WBI dose of 50Gy/25Fx with a boost of 10Gy/5Fx on the universal survival curve. Seventy-seven patients with 75 analyzable over 5 dose cohorts; 30Gy, 32.5Gy, 35Gy, 37.5Gy, and 40Gy in 5 fractions, were included in this phase I dose escalation study that started in 2010. At a median follow-up of 26.1 months, ten patients had developed fat necrosis which was associated with larger PTV volumes, with a cutoff point of 124 cm^3 or higher noted to have a higher probability of being associated with fat necrosis across dose levels. Only 1 dose-limiting toxicity was encountered and MTD was not reached, with most patients reporting excellent or good cosmesis (Rahimi IJROBP 2017). Following the report of the

safety and feasibility of adjuvant S-PBI 40Gy/5Fx, UTSW has begun investigating single-fraction adjuvant S-PBI in a dose escalation study, with the results eagerly awaited.

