## 4.3 Concomitant Medications/Treatments

### 4.3.1 Systemic and Adjuvant Surgery

#### Systemic Therapy

Use of endocrine therapy after pre-operative radiation should be started within 21 days after pre-operative radiation, but it is encouraged to start the day after the post-radiation biopsy. Typically, for estrogen/progesterone positive patients, many will start endocrine therapy as they are waiting for surgery. Oncotype or Mammprint studies should be done on the biopsy specimen, if possible, prior to delivery of radiation if there is adequate tissue. If not, patient may require another biopsy to obtain this tissue and this will be at the discretion of the medical oncologist.

Surgery: Surgery can be done anytime from 8 to 52 weeks at the discretion of the surgeon. Sentinel lymph node biopsy can be done at time of lumpectomy or if patient prefers mastectomy.

Sentinel lymph node mapping: in the previous University of Maryland pre-operative study there were no instances of failed sentinel lymph node mapping on the 25 patients treated on the trial. Based on this experience, we have no reason to think that there should be an increase in failed mappings with the pre-operative radiation treatment. A peri-tumoral, intra-dermal or peri-areolar injection are allowed based on the discretion of the breast surgeon.

Sentinel lymph node mapping exclusions: In the elderly population (defined differently in by different trials and also based on medical comorbidities), a sentinel lymph node procedure is often not performed on low-risk patients. In this trial, we will not require women 70+ to have a sentinel lymph node mapping if it is deemed unnecessary by their treatment team. This must be documented in the patient's medical record.

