### **5.2.4 1 month after Surgery**

Optional Blood Samples

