#### Secondary Endpoints

Secondary endpoints for the phase I portion of this study include cosmetic outcome as evaluated by patient and physician. In addition, the following endpoints will be evaluated as secondary endpoints:

- Local Control
- Acute Toxicity (90 Days)
- Late Toxicity (24 months)
- Rates of Surgical Morbidity
- Pathologic Complete Response Rates
- Patient and Physician Cosmesis Outcomes
- Distant Disease-Free Survival

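### After day 90 the protocol has no rule for recording non-serious wound complications attributed to surgery, so the surgical morbidity endpoint can be understated

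*Protocol*

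**What the plan says.** **Endpoint.** Protocol 2.2 and 10.1 list "Rates of Surgical Morbidity" as a secondary objective and endpoint without defining it further. Section 4.1.10 names increased surgical morbidity as the second risk of the study and mentions wound healing and seromas.

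**Timing.** Section 4.3.1: "Surgery can be done anytime from 8 to 52 weeks at the discretion of the surgeon". Section 8.1 gives the same interval. In 7.2.1, events from radiation "through 90 days post treatment will be considered acute adverse events". The note in 7.2 has adverse events documented from consent to the end of that acute period.

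**Late rule.** The paragraph of 7.2.1 on the late period reads: "After the 90 day acute period, we will only follow for grade 2 or higher toxicity: skin, rib/bone, bone (fracture), pulmonary (radiation pneumonitis". The sentence goes on to neurological toxicity and "any grade 4 or 5 toxicity deemed definitely attributed to the therapy".

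**Schedule.** Section 5.2.4 (1 month after surgery) contains one item, "Optional Blood Samples". In the 5.4 table the toxicity row is marked at 1, 3, 6, 12, 24 and 36 months after radiation. It is blank at surgery and at 1 month after surgery.

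**Reporting list.** Section 7.2.1 also lists definitely related acute and late toxicities to be reported, under "Grade 4 or higher toxicity in the below categories". Fat necrosis is on that list. The DLT definition printed just above it starts at grade 3.

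**Broader wording elsewhere.** The note in 7.2 covers late events attributed possibly, probably or definitely to treatment. Section 7.1.1 says that other treatment-related toxicity will be captured and graded, with no limit of grade or time.

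**The concern.** Most of the permitted surgery window lies in the period when the protocol narrows what is followed. Seroma, wound infection, dehiscence, re-operation and fat necrosis are not on the late list. The skin paragraph in 7.1.1 names fibrosis, rash, blistering, ulceration and telangiectasia, but no wound complication. The one time point tied to the operation has no adverse-event check.

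Whether a patient's wound morbidity is recorded may therefore depend on which side of day 90 the operation falls, and the surgeon chooses that date. Site staff who follow 7.2.1 literally would have no reason to record a grade 2 seroma after an operation in month 5. A later analysis plan cannot recover events that were never collected, so a stated endpoint, which is also a named risk, would rest on incomplete data.

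**Working it through.** The protocol states no rate, sample size or precision for surgical morbidity, so there is no figure to reproduce. The check is date arithmetic and a comparison of passages.

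**1. Surgery window against the acute period**
- Window (4.3.1, 8.1): 8 × 7 = day 56 to 52 × 7 = day 364, which is 308 days.
- Up to day 90: 90 − 56 = 34 days; 34/308 = 11%.
- After day 90: 308 − 34 = 274 days; 274/308 = 89%.
- Assuming a 30-day post-operative period, all of it lies in the acute period only if surgery is done by day 90 − 30 = 60, that is 4/308 = 1.3% of the window.

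These are shares of the window, not of patients.

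**2. Gap to the next scheduled evaluation**
- Surgery just after the 6-month visit: 365 − 183 = 182 days to the 12-month visit.
- At the extremes of the visit windows in 5.4 (6 months − 21 days, 12 months + 60 days): 425 − 162 = 263 days.

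**3. Which late events have a recording rule**

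| Event after day 90 | 7.2.1 late list | 7.1.1 and note in 7.2 |
|---|---|---|
| Skin, rib/bone, pulmonary, neurological, grade 2+ | followed | captured if attributed to treatment |
| Other event attributed to treatment, grade 1-3, not serious | not followed | captured under 7.1.1; under 7.2 it depends on whether documentation is limited to serious events |
| Wound complication attributed to surgery alone, not serious | not followed | not covered |

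The second row is a contradiction. The third row is a gap on every reading. Serious events are reportable to the DSMC under 7.3.1.

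**4. Possible size**

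Observed rate = p × [1 − s × (1 − k)], where p is the true morbidity rate, s the share of morbidity arising after day 90, and k the share of that still recorded. The documents give none of the three. With p = 20% assumed:

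| s | k | Observed |
|---|---|---|
| 0.25 | 0 | 15% |
| 0.50 | 0 | 10% |
| 0.50 | 0.5 | 15% |
| 0.89 | 0 | 2.2% |
| 0.89 | 0.5 | 11.1% |

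**5. Fat necrosis**

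Section 1.2 reports for the 5-fraction adjuvant trial that "ten patients had developed fat necrosis which was associated with larger PTV volumes". With 75 analyzable patients, 10/75 = 13.3%; grades are not given. In the present protocol the adverse-event rules name fat necrosis only in the grade 4 list. The physician cosmesis form (Appendix IV) scores it 0, 1 or 2, which is not a CTCAE grade, and 5.4 schedules that form only at baseline and 36 months.

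**The case against.** The strongest reply is that late capture is wider than 7.2.1 suggests. Section 7.1.1 captures other treatment-related toxicity, and the note in 7.2 covers late events attributed even possibly to treatment. All SAEs in the monitoring period go to the DSMC (7.3.1), and seriousness does not require relatedness (7.2.1). Some wound problems could be graded as skin, since ulceration and blistering are named there. Surgical oncology notes are a permitted source, and evaluations continue at 6, 12, 24 and 36 months. All of this stands, so a reader should not infer that everything below grade 4 goes unrecorded after day 90. It does not close the gap: the broader wording is confined to events attributed to treatment, and a permitted source does not widen the set of events to be followed.

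Three further inferences are tempting and are not supported:
- **That 89% of patients would be affected.** This needs surgery dates spread evenly over the window, and the documents give no distribution. The 5.4 table places surgery and the visit one month after it before the 3-month column, which hints at early surgery without requiring it.
- **That rates will differ artificially between dose levels.** Nothing shows that surgery timing would vary by dose, and 10.3 plans descriptive incidences with confidence intervals.
- **That the earlier trial's fat necrosis proportion applies here.** It comes from adjuvant 5-fraction treatment at a median follow-up of 26.1 months and was linked to larger target volumes. Section 1.2 presents pre-operative treatment as using smaller volumes and removing irradiated tissue. Fat necrosis also bears on late toxicity, not on surgical morbidity.

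Dose escalation is not at risk from this point: DLTs are part of the scheduled toxicity evaluations (5.4) and are separately verified (10.1).

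**Conclusion.** The point holds in a limited form. The late rule in 7.2.1 conflicts with 7.1.1 and 7.2. Non-serious wound complications attributed to surgery alone have no recording rule after day 90, and no evaluation is tied to the operation. Recorded surgical morbidity can therefore be understated; the documents do not show that it will be.

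The direction follows from the text. The size does not, because it depends on when surgery is done and on what is taken from surgical notes. With an assumed true rate of 20% and no late recording, the observed rate runs from 15% down to about 2% as the share arising after day 90 goes from 25% to 89%. Partial recording moves it back up.

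The fat necrosis threshold is a separate, smaller weakness in the late-toxicity endpoint. The severity is should-fix: this is a descriptive secondary endpoint in a phase I trial, and the 90-day DLT rule is untouched, but data not collected prospectively may be unrecoverable.

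**What to change.** 1. Add the toxicity/AE evaluation to the existing 1-month-after-surgery time point in 5.2.4 and in the 5.4 table. Footnote 1 already allows telehealth there.
2. In the late-event list of 7.2.1, add surgical and wound complications regardless of attribution, and fat necrosis. State that surgical morbidity is counted from the date of surgery, whether or not that falls after day 90.
3. Reconcile 7.1.1, the note in 7.2 and both lists in 7.2.1 so that one rule says which late events are documented. Include the mismatch between the grade 4 reporting list and the DLT definition, which starts at grade 3.

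The cost is one more adverse-event form per patient at a time point that already exists, and slightly more data entry. Dose levels, the escalation rule and the timing of surgery do not change.
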